**Research protocol: part 1**

**Project summary**

Type II diabetes mellitus (T2DM) is a progressive metabolic disorder associated with impaired glycemic control, insulin resistance, and elevated cardiovascular risk. Exercise is a well-established non-pharmacological therapy; however, the optimal sequencing of aerobic and resistance training in concurrent exercise programs remains unclear. Clarifying whether exercise order influences cardiometabolic adaptations is essential for refining exercise prescriptions in T2DM management.

The objective of this randomized controlled trial is to investigate the effect of exercise sequence on cardiovascular function and biochemical biomarkers in patients with T2DM. Specifically, the study compares the effects of aerobic–resistance versus resistance–aerobic training sequences on insulin resistance, glycemic control, lipid profile, and cardiovascular function.

A total of 39 men and women aged 41–60 years are recruited and randomly allocated into three groups: concurrent aerobic–resistance training (CART), concurrent resistance–aerobic training (CRAT), and a non-exercising control group (COT). Allocation is stratified by age and sex. The intervention spans 12 weeks, with supervised exercise sessions conducted three times per week. In CART, aerobic exercise precedes resistance training, whereas in CRAT, resistance exercise precedes aerobic training. The control group maintains standard care without structured exercise.

The primary outcomes include changes in cardiovascular function and biochemical biomarkers response. Secondary outcomes include anthropometric indices (BMI, body fat percentage, and waist–hip ratio).

This trial is expected to demonstrate that concurrent training improves metabolic and cardiovascular health in T2DM patients, with potential sequence-specific effects. Findings provide practical evidence for optimizing exercise prescriptions and enhancing the clinical management of T2DM

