**Measurement of biochemical variables**

Blood samples will be drawn from the antecubital vein both before and after the 12-week exercise training period. 48 hours after the most recent training session, blood samples will be taken to minimize the acute effects of exercise and ensure accurate results. In addition, participants must refrain from eating or drinking alcohol and coffee for 12 hours before the blood sample test, as well as avoid consuming alcohol or eating a high-fat diet.

The blood samples will be collected by a medical laboratory technician from Debre Markos Referral Hospital, who was trained in the procedure. A trained technician will utilize a venipuncture to extract blood from the antecubital vein while the participants will be seated. These samples will then be analyzed to evaluate various biochemical parameters. With some careful planning and preparation, a single blood draw will be used to acquire the sample to evaluate all of the biomarkers (HbA1c, Insulin Sensitivity, Glucose Tolerance, HDL, LDL, TC and Triglycerides) based on preplanned standard operating procedures.

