**Venipuncture Procedure**

Position the patient comfortably in a seated position, with the arm fully extended and the palm facing upward. Select an accessible vein, typically in the antecubital fossa, while avoiding areas with bruises, scars, or inflammation. Apply a tourniquet 3–4 inches above the venipuncture site and check for an easily accessible vein. Clean the site thoroughly using an alcohol swab in a circular motion, starting from the center and moving outward, and allow it to air dry completely. Press the vein by holding the skin with your thumb below the puncture site, and insert the needle bevel side up at a 15–30-degree angle.

For sample collection, follow the correct order of draw to avoid cross-contamination by collecting blood in a serum separating tube (SST) for the fasting insulin, lipid profile. Ensure sufficient blood volume is collected for all tests, typically 5 mL per tube for serum tests and 2–3 mL for HbA1c. Invert the tubes as needed for proper additive mixing, and label each tube immediately with the patient’s name, date of birth, date, and time of collection.

Since Debre Markos lacks a facility for fasting insulin level tests, the blood samples will be securely transported to the Wudassie Diagnostic Center in Addis Ababa for analysis. After collection, the fasting insulin sample will be placed in a serum separator tube (SST) and immediately labeled with the patient's information, date of birth, and time of collection. The sample will be stored in a cool, insulated container with an ice pack to maintain its integrity during transport. The sample should be delivered promptly to the diagnostic center to ensure accurate results, ideally within 24 hours. Upon arrival at the laboratory, the sample will be processed according to standard procedures for insulin level testing.

The Enzyme- Linked Immunosorbent Assay (ELISA) assay type China (Shakil-Ur-Rehman et al., 2017) will be used for the fasting insulin test assays.

The homeostasis model of insulin resistance (HOMA-IR index), which is the product of glucose and insulin concentrations divided by a factor, will be used to quantify insulin resistance (Vogeser et al., 2007). The HOMA-IR index will be calculated as:

$$HOMA-IR=\frac{fasting serum glucose (mg.\mathrm{dL}^{-1})*fasting serum insulin(\mu U.{mL}^{-1})}{405}$$

*Equation 4* *Homeostasis model of insulin resistance equation*

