**Measurement of cardiovascular function variables**

**Blood pressure**

The procedure for accurately measuring blood pressure and arterial stiffness using via an automated Sphygmocor XCEL device (AtCor Medical, CardieX, Sydney, Australia) (De la Torre Hernández et al., 2021), was adapted from Mengistu et al. (2025).

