**Procedure**

- **Cuff Placement:**
  - Place the cuff on the participant’s left upper arm, positioning it so that the artery marker aligns with the brachial artery.
  - Ensure the cuff is snug but not excessively tight, and the lower edge is approximately 2-3 cm above the elbow crease.
- **Positioning:**
  - Position the arm with the cuff at heart level for accurate readings. Use cushioning if needed to maintain proper positioning.
- **Initiating the Measurement:**
  - Begin the measurement by activating the SphygmoCor XCEL system.
  - The device will automatically record the brachial blood pressure (SBP and DBP) during cuff inflation and deflation.
- **Instructions During Measurement:**
  - Instruct the participant to remain still and refrain from speaking or moving during the cuff inflation and waveform measurement phases.
- **Post-Measurement**
- Remove the cuff and assist the participant to sit up if needed.
- Record the measurements displayed by the device:
  - Brachial SBP and DBP
  - Resting heart rate
- Conduct the measurement three times to ensure accuracy, adhering to standard protocols, and use the average of the remaining two readings.

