**Data management and statistical analysis**

All data will be systematically coded and entered into a secure, password-protected database for computer-assisted analysis. Data handling procedures include double-entry verification and regular monitoring to ensure accuracy, completeness, and consistency. Any discrepancies or spurious entries will be flagged and resolved through cross-checking with source documents.

Statistical analysis will be performed using SPSS version 27. The primary analytical approach is Repeated Measures Analysis of Covariance (RM ANCOVA), which allows for the evaluation of time-dependent changes across intervention groups while controlling for dietary practice as a covariate. This adjustment accounts for individual variability in nutritional habits that may influence metabolic outcomes.

The model will assess:

- **Main effects of time** (pre- vs post-intervention),
- **Main effects of group** (CART, CRAT, COT),

Assumptions of normality, homogeneity of variance, and sphericity will be tested prior to analysis. Violations will be corrected using appropriate statistical adjustments (e.g., Greenhouse-Geisser correction). The level of significance is set at *p* < 0.05, and partial eta squared (η²) will be reported to indicate effect sizes.

The sample size of 39 was determined through power analysis, targeting 80% power to detect moderate effect sizes in insulin resistance and cardiovascular outcomes, with a 5% significance level and allowance for 10% attrition.

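### No single primary outcome or contrast is named: about ten measures share one 5% level (about 23-40% chance of a false positive). Separately, glucose tolerance cannot come from the single fasting draw

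*Protocol*

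**What the plan says.** The Project summary defines the primary outcomes by domain: "The primary outcomes include changes in cardiovascular function and biochemical biomarkers response". Only the anthropometric indices are secondary. No measure, time point or contrast is singled out.

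The content of the two domains has to be read from the methods:

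- Measurement of biochemical variables lists seven biomarkers: "HbA1c, Insulin Sensitivity, Glucose Tolerance, HDL, LDL, TC and Triglycerides". All come from one sample per visit, taken after a 12-hour fast: "a single blood draw will be used to acquire the sample to evaluate all of the biomarkers (HbA1c, Insulin Sensitivity, Glucose Tolerance".
- Venipuncture Procedure adds that the HOMA-IR index "will be used to quantify insulin resistance". Its formula multiplies fasting glucose by fasting insulin.
- The blood-pressure Procedure records "Brachial SBP and DBP" and "Resting heart rate".
- The Blood pressure section opens with "The procedure for accurately measuring blood pressure and arterial stiffness", but arterial stiffness is not among the values to be recorded.

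In Data management and statistical analysis, "The level of significance is set at" p < 0.05, and the effects listed are the main effects of time and of group. No hierarchy or division of the 5% is given. The sample-size sentence names insulin resistance and cardiovascular outcomes together, without choosing between them.

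**The concern.** A primary outcome is meant to fix, before the data are seen, which result decides the trial. Here almost everything measured is primary, so a significant result on any one measure could be presented as the primary finding. The protocol intends its results to inform exercise prescription and policy. It also records that trial registration was completed during the intervention, so no prospective registry entry restrains the choice of what to emphasise.

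A second, unrelated defect lies in the same list. Glucose tolerance describes the response to a glucose load. A single fasting sample has no load and no later time point, so a listed primary measure cannot be obtained as described. Fasting glucose, which the HOMA-IR formula needs, is absent from the list.

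**Working it through.** **Plan's own figure.** The protocol states no overall error rate, so there is none to reproduce. Its one related figure, N = 39, cannot be reproduced uniquely because no numeric effect size, pre-post correlation or test is given. Taking moderate to mean f = 0.25 and testing group by time, 80% power needs 42 patients (42/0.9, so 47 enrolled) at correlation 0.5, or 36 (36/0.9 = 40) at correlation 0.6. The stated number is therefore plausible for one outcome under favourable assumptions.

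**Count of primary measures.** Seven biomarkers + SBP + DBP + resting heart rate = 10. HOMA-IR is treated as the listed insulin sensitivity item and not counted twice. Arterial stiffness would make 11.

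**Chance of at least one false positive.** Assume no true effects, one between-group test per measure, and 5% for each. For k independent measures the chance is 1 − 0.95^k:

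| Measures | Chance |
|---|---|
| 9 (without glucose tolerance) | 1 − 0.95^9 = 0.370 |
| 10 | 1 − 0.95^10 = 0.401 |
| 11 (with arterial stiffness) | 1 − 0.95^11 = 0.431 |

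The measures are surely correlated, but the protocol gives no values. A simulation of 6,000 null trials per setting (three arms of 13, ten equally correlated outcomes) gave:

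| Assumed correlation | Any three-arm F-test significant | Any CART versus CRAT test significant |
|---|---|---|
| 0 | 0.40 | 0.40 |
| 0.3 | 0.36 | 0.35 |
| 0.5 | 0.29 | 0.29 |
| 0.7 | 0.23 | 0.20 |

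**Cost of keeping all ten primary with Bonferroni.** Each test would use 0.05/10 = 0.005. For group by time at f = 0.25 with 39 evaluable patients, power falls from 0.77, 0.86 and 0.94 to 0.42, 0.56 and 0.74 at pre-post correlations of 0.5, 0.6 and 0.7. Adjustment alone would therefore undercut the sample size.

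**Power of a single sequence contrast.** For CART versus CRAT with 13 per arm, assumed d = 0.5, two-sided 5%, normal approximation and no baseline adjustment: 0.5 × √(13/2) = 1.275, and 1.275 − 1.96 = −0.685, which gives power of about 0.25. With 12 per arm it is 0.23. Reaching 80% would need 63 per arm.

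**Blood draw.** Neither the biochemical section nor the venipuncture section describes a glucose load or a timed second sample. The detailed procedure covers fasting insulin, lipids, HbA1c and the HOMA-IR calculation. Fasting glucose appears there only as a term in the formula.

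**The case against.** The strongest defence is that handling of multiplicity commonly sits in a statistical analysis plan. The Project management section assigns such a plan to the statistician, and it is not shown. That stands as far as it goes: testing each measure at an unadjusted 5% is inferred from the single stated level, and an adjustment may exist. It does not excuse the absence of a named primary outcome, which is the protocol's job and on which its sample size depends.

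Four stronger readings are tempting, and the document does not support them:

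- *A false positive headline result is likely.* With one between-group test per measure the chance stays below one half. It passes one half if all pairwise comparisons are tested at 5% (at correlations up to about 0.5), but the statistical section lists no pairwise tests. It also does so if the time effects count as headline tests (20 independent tests: 1 − 0.95^20 = 0.64).
- *A reported sequence effect would probably be noise.* The error rate under a complete null is not the probability that a given finding is false. That also depends on power and prior plausibility. The summary, moreover, speaks only of potential sequence effects.
- *The blood-draw problem adds to the false-positive risk.* It does not. Removing the measure lowers the independent-case figure from 40% to 37%.
- *Fasting glucose is not planned at all.* The HOMA-IR formula requires it, so this is an incomplete list and not an unplanned measurement.

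**Conclusion.** The point holds in two separate parts.

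First, the protocol names no single primary outcome or contrast and places about ten measures under one 5% level without a hierarchy. The resulting chance of at least one false positive is about 40% if the measures are independent and about 23-36% at correlations of 0.7-0.3, roughly five to eight times nominal. These figures rest on one between-group test per measure, no true effects, no adjustment in a plan not shown, and correlations that are assumed. The count and the absence of a named primary outcome are firm; the exact size of the inflation is less so.

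Second, glucose tolerance cannot be measured from the single fasting draw, and fasting glucose is missing from the biomarker list although HOMA-IR needs it. This is a measurement defect with no bearing on the error rate.

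Both should be corrected.

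**What to change.** 1. In the Project summary, name one primary outcome and one contrast before the masked analyst is unmasked. HOMA-IR at week 12, CART versus CRAT, two-sided 5%, is one choice. It fits the stated aim and one of the two outcomes in the sample-size sentence, but that sentence does not single it out, so the investigators must make and own the choice.
2. Make the remaining biomarkers and the blood-pressure and heart-rate measures secondary, either Holm-adjusted or reported as estimates with 95% confidence intervals and labelled exploratory.
3. In Measurement of biochemical variables, replace glucose tolerance with fasting glucose.
4. Date the change, update the registry, and disclose that it was made after enrolment began and after a registration completed during the intervention. Naming the outcome now limits selective emphasis but does not make it prospective.

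The changes are to wording and the registry record. There are two real costs. The other outcomes can no longer be claimed as primary successes. And the sequence contrast would carry the headline with only about 25% power under the assumptions above, so the protocol should say in advance that a null result would be inconclusive and not evidence that order does not matter.

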**Protocol Identifying Number:**

The protocol was identified by Debre Markos University, Sport Science Academy (Reference No. SpScAc.IRC/03/2025). Date of approval: June 01/2025. All participants provided written informed consent before enrollment. The trial registration (Registration No: PACTR202509591505325) was completed during the intervention period due to administrative delays and limited awareness of registration requirements at the time.

**Rationale & background information**

Type 2 diabetes (T2DM) is a growing global health concern and one of the most serious issues impacting human health [1]. Affecting millions of people, it is recognized as the sixth leading cause of death worldwide [2]. Weird patterns show that prevalence is increasing not only in developed countries but also worldwide regions [3]. According to the International Diabetes Federation (IDF), Ethiopia has the largest diabetic population in Sub-Saharan Africa, with 1.96 million adults aged 20 to 79 affected [4]. Alarmingly, around 40% of these individuals were unaware of their condition [5]. The disease's economic costs has risen to $200 million annually [4]IDF (2017). IDF (2017) The lack of awareness is largely due to the gradual progression of diabetes, with early-stage symptoms often being subtle or unnoticeable, making it challenging to recognize through classic diagnostic signs [6].

Effectively tackling this issue demands a proactive approach to both prevention and treatment. As outlined in the ACSM and ADA guidelines, effective diabetes management adopts a comprehensive approach, combining pharmacological treatments with non-pharmacological strategies such as regular physical activity, dietary adjustments, and appropriate medication [7, 8].

Considering factors such as efficacy, cost, potential side effects, weight gain, comorbidities, and the risk of hypoglycemia, patients should prefer non-pharmacological approaches [9]. Similarly, different researchers demonstrate regular physical exercise is a fundamental component of T2DM management, demonstrably improving glycemic control and overall well-being [10-13]. Specifically, resistance training (RT) has been shown to promote skeletal muscle growth, which contributes to fat reduction [14], and improved metabolic outcomes, including lower fasting plasma glucose (FPG), enhanced insulin sensitivity, and better glucose tolerance in diabetic patients [15]. Additionally, RT benefits lipid regulation by increasing HDL-c levels and reducing triglycerides (TG), making it an effective intervention for T2DM management [16]. Similarly, a meta-analysis and systematic review reviled that, aerobic exercise has demonstrated positive effects on markers of metabolic syndrome (MetS), including reduced fasting glucose, higher HDL-c levels, and lower TG levels [17, 18], moreover, it helps reduce systolic blood pressure (SBP), diastolic blood pressure (DBP), resting heart rate (RHR), fasting blood sugar (FBS), and body mass index (BMI), while improving oxygen saturation (SpO2) compared to the control group in individuals with T2DM [19].

While both aerobic and resistance exercise have their benefits, concurrent training (CT), which incorporates the special advantages of both, is typically recommended for the treatment of type 2 diabetes. There is evidence from numerous studies that it works. Glycated hemoglobin (HbA1c), body fat, peak oxygen uptake, cholesterol, and insulin resistance (HOMA-IR) were all found to significantly improve in people receiving concurrent aerobic and resistance exercise, according to Bassi, Mendes [20]. Similarly, Ambelu and Teferi [21] found that a combined aerobic-strength program significantly lowered body composition measures, blood pressure, and fasting blood glucose. However, despite the recognized benefits of CT, research on the optimal sequencing of aerobic and resistance exercises within this training approach remains limited and inconclusive.

Molecular bases the sequence of endurance and resistance exercise in concurrent training significantly influences responses due to AMPK-mTORC1 interferences. The aerobic-first sequence (AE-RE) enhances mitochondrial biogenesis, fat oxidation, and cardiovascular efficiency but may lead to residual fatigue, impair strength performance, and inhibit mTORC1 (mammalian target of rapamycin complex 1), limiting hypertrophy and strength [22]. Moreover, glycogen depletion from aerobic exercise reduces the intensity of subsequent resistance training, ultimately diminishing its effectiveness [23]. Conversely, the resistance-first sequence (RE-AE) maximizes strength and hypertrophy gains by preserving mTORC1 activation and neuromuscular efficiency, and research has also demonstrated that this training sequence had no impact on aerobic capacity [24, 25], however, Doma, Deakin [26] demonstrated that a resistance-first sequence may impair endurance performance due to resistance-induced fatigue and increased cardiovascular strain.

This concept is still inconclusive, while some studies indicate that the sequence of exercises in a CT program may affect cardiovascular and metabolic outcomes. For instance, Delgado-Floody, Soriano-Maldonado [27] displayed (AT + RT) significant decreases in waist circumferences (WC), but not for SBP, DBP, FPG, HDL-c and TG, all *p*>0.05 comparing to RT + AT among in women with severe/morbid obesity. Likewise, Kobayashi, Long [28] observed no significant changes in HbA1c when concurrent training was performed in an opposite sequence, whereas Church, Blair [29] observed significant changes in HbA1c with aerobic resistance sequence of exercises, despite improvements in VO2 max and fat mass.

Regarding lipid profiles, among non-diabetic patients, Flores-Moreno, Del [30] observed significant improvements in BMI, cholesterol, and glucose regulation when resistance training was followed by aerobic exercise among sedentary obese individuals. Conversely, Amare, Alemu [31] highlighted that an aerobic-first approach led to significant enhancements in lipid profiles and glycemic control in overweight and obese adults. Additionally, Azarbayjani, Abedy [32] noted improvements were observed in anthropometric measures and insulin resistance when aerobic exercise preceded resistance training, though no significant changes were observed in lipid profiles among sedentary adults.

These findings’ variation suggests that the sequence of aerobic and resistance exercises within concurrent training programs needs further research to identify the optimal sequence of exercises to maximize health benefits for Type II diabetic patients. Some studies suggest that performing resistance training before aerobic exercise enhances in healthy population fat oxidation and muscle glucose uptake, optimizing metabolic adaptations [33] and improves muscular strength and overall physical fitness [24, 34]. In contrast, an aerobic-first approach improves reducing visceral fat and inducing anabolism after exercise [35] and potentially inducing muscle fatigue [36], which could compromise resistance training performance [37]. Nevertheless, a recent systematic review and meta-analysis by Canli and Aldhahi [38] found no significant effect of exercise order on overall workout effectiveness or physiological adaptations. These conflicting findings highlight a critical gap in understanding the influence of exercise sequence on health outcomes, particularly in diabetic patients, underscoring the need for further research to determine the optimal exercise order for maximizing health benefits.

A key unanswered question is: How does the sequence of exercises in a CT program influence metabolic, cardiovascular, and anthropometric outcomes in individuals with Type II diabetes? And also, studies have highlighted the importance of conducting future research to compare the effects of different exercise sequences within CT for this special population [20, 39]. Moreover, previous research on CT for diabetic patients has not sufficiently accounted for diet as a confounding factor, which can greatly influence cardiovascular function and biochemical biomarker outcomes [40]. Understanding how exercise order impacts key anthropometric measures, cardiovascular function, and biochemical biomarkers is essential for optimizing treatment strategies.

To effectively address this gap in the literature, the study will evaluate and compare the order of exercise in concurrent training on the influence of anthropometric measures, biochemical markers, and cardiovascular function in middle-aged men with type 2 diabetes. To ensure accurate assessment of the exercise program's health impacts, participants will adhere to a strict dietary monitoring protocol [41].

